## Abstract

**Background::**

The incidence rate of prediabetes is increasing year by year. Prediabetes is a continuous ever fount of diabetes. Diabetes is closely related to intestinal flora imbalance and insulin resistance (IR). Previous studies have proved that Baduanjin can effectively improve the blood glucose and blood lipid of patients, but there is no relevant research on intestinal flora and IR. Therefore, this study focuses on the influence of Baduanjin on intestinal flora of patients with prediabetes, so as to improve the effect of IR, and finally delay or prevent the occurrence of to diabetes mellitus 2 type (T2DM).

**Methods::**

This study will recruit 80 patients who meet the diagnostic criteria of prediabetes from Hospital of Chengdu University of traditional Chinese Medicine. Eighty patients will be randomly divided into experimental group and control group, 40 cases in each group. The control group received routine lifestyle intervention, and the experimental group received Baduanjin at least 3 to 5 times a week for a total of 6 months. The researchers monitored the intestinal flora, insulin resistance index, blood glucose, blood lipid, body mass index, and other indicators after 3 months of intervention and 6 months of intervention

**Discussion::**

Based on previous studies, intestinal flora is closely related to the occurrence and development of T2DM-IR. Baduanjin can significantly improve the blood glucose and blood lipid of patients with prediabetes, and has a positive effect on the intestinal flora of the elderly and significantly improve the intestinal microecological balance. This study used randomized controlled trial to explore the control method between Baduanjin and conventional lifestyle, in order to further establish the application of Baduanjin in patients with prediabetes.

**Trial registration::**

This trial protocol has been approved by the research hospital and registered in China clinical trial registration center on July 6, 2020 (ChiCTR2000034490).

## Introduction

1

Prediabetes, defined by blood glucose levels between normal and diabetic levels, is increasing rapidly worldwide. Prediabetes is the subclinical impairment fasting blood glucose (IFG), impaired glucose tolerance (IGT), or both. Prediabetes belongs to the intermediate stage of abnormal glucose metabolism, which is itself a high-risk factor of diabetes. At this time, if proper and regular intervention is given, it can be reversed to normal population.^[1–5]^ Without intervention, 33% of IFG and 65% of IGT population will become diabetes within 6 years.^[6]^ Prediabetes not only directly lead to diabetes, but also increase the risk of retinopathy, peripheral neuropathy, hepatocellular carcinoma, and coronary heart disease.^[7–10]^ Studies have shown that 5% to 10% of people with prediabetes develop diabetes every year.^[11]^ The diabetes conversion rate of IGT alone is 4.35% to 6.35% per year.^[12]^ American ADA expert group pointed out: 70% of patients with prediabetes mellitus (PDM) will eventually turn to diabetes.^[13]^ The Daqing Research Report in China points out that the cumulative incidence of diabetes in 20 years of IGT population is higher than 90%.^[1]^ The International Diabetes Federation (IDF) predicts that the prevalence of IGT will increase globally in the next 20 years, reaching 472 million people by 2030, with the largest absolute increase in Southeast Asia and the Western Pacific. According to the 2012 statistical report, nearly 86 million adult prediabetes patients in the United States.^[14]^ According to the study of South Asia heart metabolism risk reduction center (CARRS), the prevalence of prediabetes in South Asian population was 31.1% to 47.9% in 2011.^[15]^ A cross-sectional survey in 2017 showed that the prevalence of prediabetes in Chinese adults was 35.7%.^[16]^

Prediabetes patients mainly through lifestyle intervention and hypoglycemic drug intervention. Lifestyle intervention mainly includes reasonable diet, proper physical activity, weight control, and so on. Moderate intensity physical activity (such as brisk walking) of 150 minutes/week is beneficial for patients with prediabetes.^[17]^ Moderate intensity physical activity can improve insulin sensitivity and reduce abdominal fat in children and young people.^[18,19]^ Reducing caloric intake is of paramount importance for those at high risk for developing type 2 diabetes (T2DM). Currently, no drug has been approved by the U.S. Food and Drug Administration for the prevention of diabetes. However, the 2018 ADA guidelines point out that metformin can be used for prevention of diabetes in patients with body mass index (BMI) ≥ 35 kg/m^2^, age <60 years old and with a history of gestational diabetes mellitus.^[17]^ There are still some controversies about whether to use drugs in prediabetes. Only those patients who can not adhere to healthy lifestyle for a long time or whose blood sugar still does not drop after lifestyle change should be considered to use hypoglycemic drugs.^[5]^ Lifestyle intervention is the first economic and effective intervention method for patients with prediabetes.

Baduanjin is a moderate intensity aerobic exercise. Baduanjin is based on the theory of Traditional Chinese medicine (TCM) and has a history of more than 1000 years. Baduanjin is very popular in China. Similar to the traditional Taijiquan, Baduanjin has the characteristics of slow movement and relaxation. It is easy to learn and practice and is less likely to cause harm. A set of 8 section brocade qigong practice method, in addition to the starting and stopping movements, also includes 8 movements, each of which is repeated 4 to 8 times. It usually takes about 15 to 20 minutes to complete. Some studies found that through Baduanjin, the blood glucose and blood lipid of PDM patients were significantly improved.^[20]^ Sun Hongmei has proved that Baduanjin has a positive effect on the intestinal flora of the elderly and significantly improves the intestinal microecological balance, which is mainly manifested in the increase of beneficial bacteria Bifidobacterium and Lactobacillus, and the decrease of conditional pathogenic bacteria and harmful bacteria such as Enterobacter, Fusobacterium, and Enterococcus.^[20]^ The fitness effect of Baduanjin was confirmed from the view of microbiology. However, the effect of Baduanjin on intestinal flora of patients with PDM and its correlation with insulin resistance (IR) need to be further studied.

Intestinal flora is a kind of microflora which is located in the human intestinal tract. The intestinal microflora is closely related to the energy metabolism of human body.^[21–23]^ Microbiological studies showed that there were significant differences in the number and species of intestinal flora between diabetes mellitus (DM) patients and normal people.^[24,25]^ Metabolic products produced by microorganisms and host regulation are the key factors affecting IR.^[26]^ The beneficial bacteria in the first gut can correct IR by regulating lipid metabolism of the host. Beneficial bacteria can decompose food components that cannot be digested by the host and convert them into short chain fatty acids. Intestinal probiotics can improve IR by reducing the occurrence of inflammatory reaction.^[27–29]^ In addition, intestinal probiotics can correct impaired glucose tolerance by regulating oxidative stress factors.^[30,31]^ Intestinal flora is closely related to the occurrence and development of T2DM-IR.

We designed a randomized clinical trial to study the effect of Baduanjin on prediabetic patients. The purpose of this study is to determine whether Baduanjin can change the type and quantity of intestinal flora in patients with prediabetes mellitus so as to improve the IR state, and ultimately achieve the recovery of impaired glucose regulation to normal glucose regulation in patients with PDM, effectively delay or even prevent the occurrence of T2DM.

## Methods and analysis

2

The study was registered with the China clinical trials registry (registration number: ChiCTR2000034490). This study is a randomized controlled trial. The research scheme of this research project has been approved by the local ethics committee of Hospital of Chengdu University of traditional Chinese medicine before implementation. It is in line with the provisions of the Helsinki declaration. All subjects will receive written informed consent (Fig. 1).

**Figure 1 F1:**
[figure not shown]
Study flowchart.

### Site and participant recruitment

2.1

The participants will be enrolled from Hospital of Chengdu University of traditional Chinese medicine in Chengdu, Sichuan Province: researchers will conduct trial enrollment publicity through oral publicity, hospital posters, and web ads. Recruitment starts on July 15, 2020 and is expected to be completed on August 15, 2020.

### Patient screening

2.2

Patients will be deemed eligible after screening according to the inclusion and exclusion criteria.

#### Inclusion criteria

2.2.1

According to the diagnostic criteria of prediabetes in the 2017 edition of Chinese guidelines for the prevention and treatment of type 2 diabetes mellitus (Fig. 2),^[32]^ all patients underwent oral anhydrous glucose tolerance test (OGTT). The diagnostic criteria of PDM will be as follows:

1.People whose muscle strength is grade IV or above and can complete moderate or above intensity exercise;2.Aged 18 to 70 years old;3.They did not keep the habit of regular exercise in recent 3 months (i.e., <3 times a week, each time <30 minutes);4.Clear consciousness, normal hearing, can communicate with people, understand, and follow the demonstration action;5.Sign informed consent.

**Figure 2 F2:**
[figure not shown]
Classification of glucose metabolism status. Prediabetes can be diagnosed by either impaired fasting blood glucose (IFG) or impaired glucose tolerance (IGT).

#### Exclusion criteria

2.2.2

1.Patients who have been diagnosed with DM;2.Patients with hearing impairment/consciousness impairment/cognitive impairment;3.All kinds of acute and chronic infection, stress, tumor, and other immune diseases and pregnant or lactating women;4.Those who need to take the drugs that affect the observation indicators for a long time;5.The subjects were engaged in severe physical activities;6.Unwilling to provide personal information.

### Randomization and blinding

2.3

The patients who passed the qualification assessment will randomly divide the random participants into the Baduanjin group or the routine lifestyle intervention group, and use computer-generated random numbers (FileMarker Pro) for stratification. Data analysts and key outcome assessors will blindly assign treatment assignments. However, some researchers need to conduct the Baduanjin teaching campaign and supervise the experiment, and they will know the group they are assigned to.

### Intervention

2.4

In addition to the interventions described below, all participants were required to continue their normal life and treatment (i.e., medication) during the trial. All patients participating in the study will participate in Baduanjin for 6 months.

**Figure 3 F3:**
[figure not shown]
Illustration of the 10 postures of Baduanjin.

### Sample size estimation

2.5

Our preliminary study reported that the standard deviation of intestinal microflora in patients with prediabetes was 6.28 CFU/g. At a significant level of 0.05, 80% power was required to detect blood glucose. The average difference between the 2 groups was 5.1 cfu/g. The formula for calculating the sample size is as follows: 

Therefore, we calculated at least 32 sample sizes for each study group, and expected to lose 20% in the future. After calculation, a total of 80 people were admitted.

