#### Primary outcomes

2.6.1

1.Intestinal floraThe sterile stool box will be distributed to PDM patients, and the patients were instructed to collect 5 to 10 g stool for the first time in the morning. Sterile feces will be detected by 16S fragment high-throughput sequencing. Through the relevant results of intestinal flora, the number and species of intestinal flora in patients with PDM before and after intervention will be obtained, and the results will be analyzed and compared.2.IR indexFasting venous blood samples will be collected from all participants. Fasting blood glucose (FBG) and fasting insulin (FINS) will be measured by automatic biochemical analyzer (model: AU5800) of Beckman Coulter company. The insulin resistance index (HOMO-IR) will be calculated as an auxiliary measure of insulin sensitivity (HOMO-IR = FBG × FINS/22.5).

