### Data analysis

2.9

In order to evaluate the effect of Baduanjin intervention and conventional lifestyle intervention, the results will be compared. Spss21.0 will be used for statistical analysis of all the data. The statistical analysis will take bilateral test, and take α = 0.05 as the test level. If the measurement data conform to the normal distribution, the description of 

 is adopted. If it does not meet the normal distribution, it is described by the median and quartile interval. In the result analysis, if the data conform to the normal distribution, the *t* test of 2 independent samples is used for statistical inference. The Wilcoxon Mann–Whitney rank sum test is used to infer if the distribution does not conform to the normal distribution. The counting data were analyzed by person chi square test.

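### The sample size paragraph uses a CFU/g scale and names blood glucose, neither of which matches a primary outcome as measured, and its 32 per group corresponds to about 90% power, not the stated 80%

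*Protocol article*

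**What the plan says.** Section 2.5 (Sample size estimation) gives two numerical inputs. The first is from a preliminary study: "the standard deviation of intestinal microflora in patients with prediabetes was 6.28 CFU/g". The second is the difference: "The average difference between the 2 groups was 5.1 cfu/g". Between them stands the error specification: "At a significant level of 0.05, 80% power was required to detect blood glucose". The paragraph concludes with at least 32 per group, a 20% expected loss and 80 patients in total. The abstract gives equal allocation, 40 per group.

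Section 2.6.1 lists two primary outcomes. For flora the method is "Sterile feces will be detected by 16S fragment high-throughput sequencing", and the result is described as the number and species of flora before and after the intervention. For insulin resistance, "The insulin resistance index (HOMO-IR) will be calculated as an auxiliary measure of insulin sensitivity" (the index is HOMA-IR, printed with an O). Section 2.6.2 lists fasting and 2-hour blood glucose as secondary.

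Section 2.9 fixes the sidedness: "The statistical analysis will take bilateral test, and take α = 0.05 as the test level". The test is the two-sample t test, or the rank-sum test if the data are not normal.

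**The concern.** A sample size statement should tell the reader which effect, on which primary outcome, the trial can detect. Three features of section 2.5 prevent that.

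- **Scale.** CFU/g is a colony-count unit. 16S sequencing ordinarily yields reads, relative abundances and diversity indices. The unit appears nowhere in the article outside section 2.5, and section 2.6.1 names no single flora parameter to which 6.28 or 5.1 could apply.
- **Variable.** The power is attached to blood glucose, which is neither primary nor measured in CFU/g.
- **Coverage.** HOMA-IR is listed as a primary outcome alongside flora, but the stated power does not extend to it.

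A further question is whether 32 per group follows from the stated inputs at all.

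At stake is how the results are read. If the report calls the trial powered at 80%, a null result on HOMA-IR or on a 16S index could be taken as evidence of no effect, although the plan never showed what difference on those scales it could detect.

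**Working it through.** **Inputs.** SD 6.28, difference 5.1, alpha 0.05, power 80%, 32 per group and 20% loss (section 2.5); two-sided test (section 2.9); 1:1 allocation (abstract). The printed formula is not readable in the text at hand, so the standard formula for two means is used and the missing formula is not held against the plan.

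**1. Standardised difference.** 5.1/6.28 = 0.812 SD.

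**2. The plan's n per group.** Normal approximation: n = 2(z₁₋α/₂ + z₁₋β)²/d².

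- At 80% power: 2(1.960 + 0.842)²/0.812² = 23.8, so 24 per group. The exact t test gives 24.8, so 25.
- At 90% power: 2(1.960 + 1.282)²/0.812² = 31.9, so 32 per group. The exact t test gives 32.9, so 33.

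The stated 32 is not reproduced at 80% power; it is reproduced at 90%. Other readings that keep 80% power do not reach 32 either:

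| Reading at 80% power | n per group |
|---|---|
| One-sided 0.05, normal approximation | 19 |
| Two-sided 0.05, normal approximation | 24 |
| Two-sided 0.05, t test | 25 |
| Rank-sum test, efficiency 0.955 | 26 |
| Rank-sum test, worst-case efficiency 0.864 | 29 |
| Two-sided 0.025, normal approximation | 29 |
| Two-sided 0.025, t test | 31 |

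**3. Power that 32 per group delivers at the stated inputs.** 90.1% by the normal approximation, 89.2% by the t test.

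**4. Dropout.** 32/(1 − 0.20) = 40 per group, 80 in total. This is correct. Had 80% power been carried through by the normal approximation, the result would be 24/0.8 = 30 per group, 60 in total.

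**5. What 32 evaluable per group can detect on any endpoint.** Exact t test, 80% power: 0.711 SD at two-sided 0.05, and 0.787 SD at two-sided 0.025 (alpha divided equally between two primary outcomes).

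**6. Power for smaller effects.** The article gives no SD or difference for HOMA-IR or for any 16S measure, so a corrected sample size cannot be computed. The effects below are assumptions.

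| Assumed true effect (SD) | Power, 32 per group, two-sided 0.05, t test |
|---|---|
| 0.4 | 35% |
| 0.5 | 50% |
| 0.6 | 66% |

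**The case against.** The strongest reply is that the link to a primary outcome exists: section 2.5 sizes the trial on intestinal microflora, and flora is the first primary outcome in section 2.6.1. That stands as far as the name goes. A reader might infer that the calculation has nothing to do with any primary outcome; the text does not support that. What fails is the match between the unit and the assay.

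Blood glucose is probably a slip. The sentences on either side concern flora, and no SD or difference for glucose appears. So a reader should not conclude that the trial was sized on a secondary outcome. It remains a wrong word in the sentence that defines the power.

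The article never says culture or plating; that is inferred from the unit, and the assay of the preliminary study is not described. It is also tempting to argue that the figures are biologically impossible, either trivial as raw counts or enormous as logarithms. The article states neither reading, and a scaled unit with a power of ten left out is possible, so that argument is not made here.

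A condensed article may leave a separate HOMA-IR calculation to a fuller document, so its absence alone is not the error. The error is that the one power claim made does not cover a named primary outcome and does not say so.

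Finally, one might infer that correcting the paragraph makes the power look worse. The documents do not show this. On the stated effect, 32 per group exceeds 80% power at two-sided 0.05 (89 to 90%), and also at 0.025 (83% by the t test). The lower figures depend wholly on assumed effects.

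**Conclusion.** Section 2.5 is wrong as written, on two independent grounds.

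First, its inputs are on a scale that the planned flora assay is not said to report, its power sentence names a secondary outcome, and HOMA-IR lies outside the stated power. Second, 32 per group does not follow from 80% power: the stated inputs need 24 to 25, and 32 corresponds to 89 to 90%.

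The second ground needs only the article's own figures and a standard formula. The first rests on the ordinary meaning of CFU/g and on the absence of that unit from section 2.6.1. The total of 80 follows correctly from 32 per group and 20% loss, and nothing here shows that 80 is too few or too many. That cannot be judged until an SD and a target difference are given on the scales actually measured. The point should be corrected before the results are reported, because any statement about power would rest on this paragraph.

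**What to change.** Keep 80 patients and rewrite section 2.5:

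1. Delete blood glucose from the power sentence.
2. Name one flora parameter derived from the 16S data. Either justify 6.28 and 5.1 as applying to it, or replace them with an SD and a target difference on its scale, with the source.
3. Correct the stated power to what 32 per group delivers for the stated inputs: about 90%, not 80%. If the inputs are replaced, recompute it.
4. State that for any primary endpoint, HOMA-IR included, 32 evaluable per group gives 80% power only for a difference of about 0.71 SD at two-sided 0.05, or about 0.79 SD if alpha is split between the two primary outcomes.

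The cost is one paragraph and no extra patients. The downside is that the power claim becomes conditional on each endpoint's SD.

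### The stated 80% power does not yield 32 per group: the plan's own inputs give 24 to 25, and 32 is the answer for 90% power

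*Protocol article*

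**What the plan says.** Section 2.5 (Sample size estimation) takes its variability from the authors' preliminary work: "the standard deviation of intestinal microflora in patients with prediabetes was 6.28 CFU/g". The error rates follow: "At a significant level of 0.05, 80% power was required to detect blood glucose". The effect is given as: "The average difference between the 2 groups was 5.1 cfu/g". A formula is announced but is not legible in the text at hand, and nothing here is held against that. The result is: "Therefore, we calculated at least 32 sample sizes for each study group, and expected to lose 20% in the future". The total is then set at 80.

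Two other places complete the calculation. Section 2.9 (Data analysis) fixes sidedness: "The statistical analysis will take bilateral test, and take α = 0.05 as the test level". It also names the test for normally distributed data: "if the data conform to the normal distribution, the *t* test of 2 independent samples is used for statistical inference", with a rank sum test otherwise. The Abstract gives equal allocation: "Eighty patients will be randomly divided into experimental group and control group, 40 cases in each group".

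**The concern.** Every input to a standard comparison of two means is printed, so the sample size can be recomputed without outside assumptions. The recomputation falls well short of 32. The gap is about a third of the required number, too large for rounding or for the choice between normal and t quantiles.

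Section 2.5 is the only place where the article says what the trial was sized to detect, and the trial's report will cite its power and sample size. As printed, the design could be 90% power for a difference of 5.1, 80% power for a smaller difference of about 4.4, or something else. Whoever later reads a null result against the design needs to know which. The section does not help to settle it, because it speaks of power for blood glucose while giving the standard deviation and difference in CFU/g.

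**Working it through.** **Inputs.** SD = 6.28, difference = 5.1, α = 0.05 and power = 80% (section 2.5); two-sided test (section 2.9); 1:1 allocation (Abstract).

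**Formula, per group.** n = 2 × (z for α + z for power)² × SD² / difference².

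SD² / difference² = 39.44 / 26.01 = 1.516.

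**At the stated 80% power.** n = 2 × (1.960 + 0.842)² × 1.516 = 23.8, so 24 per group. With the noncentral t distribution it is 24.8, so 25. After 20% loss: 24 / 0.8 = 30 per group (60 in total), or 25 / 0.8 = 31.25, so 32 per group (64 in total).

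**Which power gives 32?** With 1.282 in place of 0.842, n = 2 × (1.960 + 1.282)² × 1.516 = 31.9, so 32 per group (t: 32.9, so 33). The plan's figure is therefore reproduced at 90% power by the normal approximation.

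**Power at the stated sizes.** The standard error at 32 per group is 6.28 × √(2/32) = 1.57. Then 5.1 / 1.57 − 1.960 = 1.288, which gives power 0.901.

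| Evaluable per group | Power, normal | Power, t test |
|---|---|---|
| 24 | 0.803 | 0.786 |
| 25 | 0.819 | 0.803 |
| 32 | 0.901 | 0.892 |
| 40 | 0.953 | 0.948 |

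**Loss step.** 32 / (1 − 0.20) = 40 per group, 80 in total. This agrees with the plan.

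**What would make 32 the 80% answer?** By the normal approximation, either a difference of 1.57 × 2.802 = 4.40 with SD 6.28, or an SD of 5.1 / (0.25 × 2.802) = 7.28 with difference 5.1. By the t test the corresponding values are about 4.47 and 7.2.

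**Other routes to 32.** None works with α = 0.05 and 80% power:

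- One-sided 0.05: 19 per group (t: 20), further away and against section 2.9.
- Allowance for the rank sum test (relative efficiency 0.955 or 0.864, or 15% added): about 25 to 29.
- α halved to 0.025 for two primary outcomes: 29 (t: 31), and section 2.5 states 0.05.
- One-sample or paired formula: 12.
- One-sided 0.05 at 95% power: 33, against both the stated power and the stated sidedness.
- The t-based 25 inflated for 20% loss: 32. But section 2.5 presents 32 as the number before loss and inflates it again to 40, so loss would be counted twice. That would be a different error.

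**The case against.** The strongest reply is that the error is harmless. On the plan's own inputs, 32 evaluable per group gives 89% to 90% power, more than the 80% asked for, and the text offers 32 only as a minimum. The loss step is right, and no test, outcome or enrolment figure changes. This stands, provided the SD and the difference are the correct figures. If one of them is the misprint, the reassurance has to be checked again.

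A second reply is that a target difference and SD are stated, so a null result can still be read from its confidence interval against 5.1. That is fair, and it limits the damage. It does not help if 5.1 or 6.28 is itself the wrong figure, which the text leaves open.

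A third is that a slip in the power is only the likely explanation. The exact match at 90% points that way, but the formula's constants cannot be seen. This also stands, and it is why the inputs should be confirmed before the power is restated.

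None of these replies produces 32 from the stated α and power.

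**Conclusion.** The concern holds. With SD 6.28, difference 5.1, two-sided α = 0.05, equal allocation and 80% power, the requirement is 24 per group (25 by the t test), not 32. The stated number is 7 to 8 per group too high for the stated power. Equivalently, the stated power is about 9 to 10 percentage points too low for the stated number. The most likely cause is that the calculation was done at 90% power and reported as 80%, but the document does not establish this.

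The inconsistency should be corrected because these are core design figures that contradict each other. If the SD and difference are right, the trial has more power than it claims and its size can stay as it is.

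**What to change.** First check the SD, the difference and the power against the preliminary data and the formula actually used. Then change section 2.5 in one of three ways:

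1. If the SD and difference are right and the power was misreported, state that 32 evaluable patients per group give about 90% power (89% by the t test) for a difference of 5.1 with SD 6.28 at two-sided 0.05, and that 20% loss brings this to 40 per group.
2. If 80% power is the intended basis and the SD is right, state that 32 evaluable per group give 80% power for a standardised difference of 0.71, that is about 4.5 with SD 6.28 by the t test (4.4 by the normal approximation).
3. If the SD or the difference was mistyped, correct it, recompute, and confirm that 80 patients still suffice.

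In each case write two-sided in section 2.5 itself and name the outcome to which the SD and difference belong, since the section now mentions blood glucose beside CFU/g. The first two options cost one sentence and leave enrolment at 80. The third costs a recalculation.
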